#### Exclusion criteria for HCs

Participants in the HCs group will exclude: (i) those with serious diseases of the heart, brain, liver, kidneys, and other vital organs; (ii) have a mental or physical disability; (iii) those with a suspected or actual history of alcohol or drug abuse; (iv) contraindications to MRI (e.g., metallic foreign bodies, vascular stents, pacemakers, dentures, claustrophobia, etc.); (v) pregnancy and breastfeeding; and (vi) populations with possible differences in brain structure and function, e.g., smoking or alcohol addictions.

### Randomization and blinding

All MWoA participants will be randomly assigned in a 1:1:1 ratio to one of three groups: Group A (CAT group), Group B (IAT group), and Group C (sham CAT group). Random numbers will be generated using a computer and sealed in opaque envelopes by an independent research assistant. After acceptance of the random allocation principle, participants will randomly select an opaque envelope to receive an allocation serial number, which will be recorded on a Case Report Form (CRF) by a dedicated research assistant. To maintain blinding, the researchers, assessors, and statistical analysts will be separated throughout the study. Due to the specific nature of the sham acupuncture operation, it will be difficult to blind the acupuncturists during the treatment. They will receive training from the investigator and will be instructed not to disclose the allocation of participants unless there are exceptional circumstances, such as severe infection or uncontrollable pain. During treatment, participants will be accommodated in separate rooms to minimize communication.

### Interventions

Healthy controls will not undergo any treatment during the trial period, brain imaging data will be collected only once. Based on Traditional Chinese Medicine (TCM) theory, which suggests that most migraines are associated with temporal headaches, and following the findings from our previous studies on acupuncture for MWoA (Li et al., 2022, 2023), we have selected six frequently used acupoints along the Shaoyang meridian. These acupoints include Fengchi (GB20), Shuaigu (GB8), Waiguan (TE5), Zhongzhu (TE3), Yanglingquan (GB34), and Zulinqi (GB41). The positioning of these acupoints will be determined according to the standards set by the WHO Standard Acupuncture Point Locations in the Western Pacific Region (2008) (WHO Regional Office for the Western Pacific, 2008). Locations of the acupoints are presented in Table 2 and Figure 2. The interventions are compliant with the Consolidated Standards of Reporting Trials (Schulz et al., 2010) and the Standards for Reporting Interventions in Clinical Trials of Acupuncture (MacPherson et al., 2002). Patients will be instructed to assume a prone position with the head and face down, thus obscuring their vision during the acupuncture procedure. Then, the acupuncturist will routinely disinfect the skin around the acupoints.

**TABLE 2 T2:** Location of acupoints.

Acupoints	Location
GB20 (Fengchi)	In the anterior region of the neck, inferior to the occipital bone, in the depression between the origins of sternocleidomastoid and the trapezius muscles.
GB8 (Shuaigu)	On the head, directly superior to the auricular apex, 1.5 B-cun superior to the temporal hairline.
TE5 (Waiguan)	On the posterior aspect of the forearm, midpoint of the interosseous space between the radius and the ulna, 2 B-cun proximal to the dorsal wrist crease.
TE5 (Waiguan)	On the posterior aspect of the forearm, midpoint of the interosseous space between the radius and the ulna, 2 B-cun proximal to the dorsal wrist crease.
GB34 (Yanglingquan)	On the fibular aspect of the leg, in the depression anterior and distal to the head of the fibula.
GB41 (Zulinqi)	On the dorsum of the foot, distal to the junction of the bases of the fourth and fifth metatarsal bones, in the depression lateral to the fifth extensor digitorum longus tendon.

**FIGURE 2 F2:**
[figure not shown]
Location of acupoints.

### CAT group (Group A)

Patients in this group will receive acupuncture treatment at the acupoints on the contralateral side of the headache. The acupuncture [0.30 × (25 mm, 40 mm) Hua Tuo, Suzhou, China] will be used in this group. The PSD (see Figure 3; Li et al., 2022) will be fixed to the acupoints and the direction of needling is oblique downwards at GB 20, the level at GB 8, and straight at the rest of the acupoints. Due to the presence of hair on the head, the PSD may not adhere easily, so the needle will be secured in place with a hair patch. After needling the acupoints, the needle will be twisted 90–180° and lifted and inserted by 3–5 mm to induce a *deqi* sensation. The needles will be retained for 30 min, with needle manipulations performed every 15 min during this period.

**FIGURE 3 F3:**
[figure not shown]
Park sham acupuncture device.

### IAT group (Group B)

Patients in this group will receive acupuncture treatment at acupoints on the same side as their headache, following the same procedures as Group A.

### Sham CAT group (Group C)

This group will receive treatment with non-penetrating retractable blunt needles [0.30 × (25 mm, 40 mm) Hua Tuo, Suzhou, China]. During the procedure, the blunt needle will retract the hollow shank when it touches the skin, without piercing the skin (see Figure 3). However, patients will experience the sensation of being pricked by the needle. The blunt needle will also be secured with a hair patch at the head acupoints (Li et al., 2022). The needles will be retained for 30 min without any further manipulations.

All patients will receive 3 treatments per week, for a total of 24 treatments in the study. The operation will be performed by two acupuncturists with at least 3 years of clinical experience. Follow-up visits will be conducted every 4 weeks throughout the study, up to week 16.

### Urgent treatment with medication

Throughout the study, for the emergency treatment of acute migraine attacks in migraine patients, we will give the recommended NSAIDs for acute migraine attacks: ibuprofen (200–400 mg/times, not more than 800 mg/day) or diclofenac (50–100 mg/times, not more than 150 mg/day) according to the Chinese Migraine Diagnosis and Treatment Guidelines (2022 edition) (NBoCMD Association and HaSDSCotCRH Association, 2022), the types of drugs and dosage will be based on the patient’s needs and the doctor’s recommendation. However, they will not be allowed to use any prophylactic medications. Details such as the medication name, dosage, administration time, and the time taken for pain relief should be documented for any medication used.

### Sample size calculation

Regarding the sample size calculation for the modulation of brain functional networks by acupuncture, there is no established method. However, in line with the requirements of brain functional network analysis techniques (Bossier et al., 2020), a sample size of 30 cases per group should provide relatively stable reproducibility. We plan to include 30 cases in each treatment group, and with an estimated loss rate of 8%, we will aim for 32 cases per group, resulting in a total of 96 cases. The HCs group will consist of 30 cases, as they are undergoing examinations only once and are generally not participants in loss.

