### Seed-based FC analysis

The seed-based FC analysis will include all MWoA and HC participants and who completed the entire trial. PAG plays a pivotal role in the context of acupuncture for migraine treatment, so the PAG was chosen as the ROI for FC analysis. The location of the PAG seed will be selected based on previous studies (MNI coordinates: 0, −32, −12; size: 6 mm radius sphere) (Kucyi et al., 2013; Coulombe et al., 2017). The time course of each voxel in PAG will be extracted and averaged. Pearson correlation coefficients will be calculated between the average time series of PAG and each voxel throughout the whole brain. The obtained correlation coefficients will undergo Fisher-Z-transformed to increase normality. A clusterwise family-wise error rate (FWE) correction will also be considered.

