### Neuroimaging data analysis

The structural MRI data will be analyzed using the VBM toolbox within SPM12. The steps will include interlaminar time difference correction, spatial difference correction, head motion correction, normalization, and Gaussian smoothing (Yao et al., 2021). During head motion correction, images of participants with translations of less than 1 mm and rotational movements of less than 2° will be involved in the subsequent analysis. The MRI data will be analyzed using PANDA, GRETNA and BrainNet Viewer toolboxes and SurfStat. In VBM analysis, generalized linear regression model analysis will be used and between-group VBM comparisons will be made using corrected subject migraine attack intensity, migraine attack frequency, etc. (control covariates: age, PSQI, SAS, SDS, etc.) and total intracranial volume by two-sample *t*-test. A significant difference between groups will be indicated when *p* < 0.05 (FWE corrected). Only collections with more than 20 voxels will be considered as statistically significant brain regions. First, the FC of PAG in the baseline session will be compared between the migraine patients and normal participants using two sample *t*-test with FWE correction. Second, two-factor three-level mixed design ANOVA (Time: baseline and after treatment; Treatment: CAT, IAT, and sham CAT) will be conducted on migraine patients to explore the effect of treatment schedule on the FC of PAG after FWE correction. *Post hoc* analysis will be implemented using paired *t*-test to investigate the alteration of FC between before and after treatment for each treatment schedule. Finally, Pearson correlation analysis will be performed between the change in VAS score and the changes of FC in significant regions for three treatment schedules, respectively. The statistical analysis for the VBM will follow a similar procedure to that for the FC of PAG.

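### At the stated 8% loss, 32 per arm leaves about 29 rather than 30, and neither patients nor healthy controls have a margin for scans removed by the head-motion rule

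*Protocol article*

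**What the plan says.** The Sample size calculation section of the protocol article says that no established method exists for this kind of imaging study and falls back on a rule for brain network analysis: "a sample size of 30 cases per group should provide relatively stable reproducibility". It continues "We plan to include 30 cases in each treatment group", and then "with an estimated loss rate of 8%, we will aim for 32 cases per group", "resulting in a total of 96 cases". No effect size, standard deviation or power is given, so the 30-per-group rule is the only justification offered.

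Healthy controls get no allowance: "The HCs group will consist of 30 cases, as they are undergoing examinations only once and are generally not participants in loss".

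The Neuroimaging data analysis section then sets a motion limit: "images of participants with translations of less than 1 mm and rotational movements of less than 2° will be involved in the subsequent analysis". The same section plans a comparison of patients with controls at baseline, and a mixed ANOVA and paired tests on patients scanned before and after treatment.

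**The concern.** A target, a loss rate and an enrolled number are all stated, so a reader can check whether the third follows from the first two. It does not quite.

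The target concerns the reproducibility of imaging analyses, so the count that matters is patients and controls with usable scans. The reason given for adding no controls is that they attend once and so are not lost. That reads loss as drop-out. A scan spoiled by movement is a different event: it can happen to someone who completes everything, including a control at a single visit. Patients contribute to the before-and-after analyses through two scans and so have two occasions to fail the limit.

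At stake is the one figure that supports the trial's size. If it is not met, the imaging comparisons, including the first planned contrast of patients with controls, rest on fewer cases than readers are told to expect.

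**Working it through.** **Inputs from the article.** Target 30 per treatment group, loss 8%, enrolled 32 per group, 96 in total, 30 controls with no allowance (all Sample size calculation); 1:1:1 allocation (Randomization and blinding); two-tailed tests at 0.05 (Clinical data analysis).

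**Input not in the article.** The share *m* of remaining participants whose scans fail the motion limit. I assume 3%, 5% and 10%.

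**1. The plan's own figure.**
- Total: 3 × 32 = 96, as stated.
- Inflation by division: 30 / (1 − 0.08) = 32.61, rounded up to 33 per arm, or 99 in total.
- Inflation by multiplication (the less exact habit): 30 × 1.08 = 32.4. This gives the stated 32 only by rounding down.
- Back-check: 32 × 0.92 = 29.44 expected per arm, short of 30 by 0.56 of a patient.
- Largest loss that still leaves 30 of 32: 2 / 32 = 6.25%.

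**2. Chance of keeping 30.** With independent losses at 8%, P(at least 30 of 32 remain) = 0.52 in one arm and 0.52³ ≈ 0.14 in all three. With 33 per arm the same quantities are 0.73 and 0.39. One more patient per arm helps but would not secure 30 either.

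**3. Adding motion exclusions for patients.** Expected usable per arm = 32 × 0.92 × (1 − *m*):

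| *m* (assumed) | Usable per arm from 32 | Enrolment per arm to expect 30 |
|---|---|---|
| 3% | 28.6 | 34 |
| 5% | 28.0 | 35 |
| 10% | 26.5 | 37 |

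The last column is 30 / [0.92 × (1 − *m*)], rounded up.

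**4. Healthy controls.** Expected usable = 30 × (1 − *m*): 29.1, 28.5 and 27.0 at 3%, 5% and 10%. The chance that all 30 are usable is (1 − *m*)³⁰ = 0.40, 0.21 and 0.04.

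**5. The primary VAS outcome, for reference.** The smallest difference detectable with 80% power by an unadjusted pairwise two-sample t-test at two-sided 0.05 is 0.71 SD with 32 per arm and 0.75 SD with 29. The Clinical data analysis section plans intention-to-treat analysis with multiple imputation, so 32 is the size of the analysis set. Imputation does not restore all the lost information, so the effective figure lies between the two.

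**The case against.** The strongest reply is that the rounding gap is trivial. It is 0.56 of an expected patient, or one enrolled patient per arm; 32.4 rounds to 32 under a common convention; and the target is worded as a soft rule, with no guarantee of 30 evaluable cases. Nothing in the article suggests that 29 per group would be less reproducible than 30. All of this stands. It also means that the 0.52 and 0.14 probabilities should not be over-read, because they treat 30 as a cliff and even 33 per arm does poorly by that test.

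On scan failures, the reply is that the article never expressly says the 8% leaves them out, that foam restraint is used to limit motion, and that further acquisition and preprocessing steps are in a supplementary file not seen here, which might provide for repeat scans. This stands in part. That the 8% means drop-out is an inference, though the reason given for the control group supports it strongly. The article does not say what happens when only one of a patient's two sessions fails, and the size of any shortfall is unknown.

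Three stronger readings are tempting but not supported:
- The Seed-based FC analysis section restricts that analysis to completers, which a reader might count as a further source of loss. For patients, non-completers are the same people as the 8%, so counting both would be double counting.
- The requirement of 72 attack-free hours before a scan (MRI data) leads to rescheduling, so it is not an exclusion.
- A reader might apply the reduced imaging numbers to the VAS comparison. The motion rule concerns imaging only; the clinical analysis is by intention to treat.

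**Conclusion.** Wrong as written, and modest in size. On the section's own inputs, 32 per arm gives an expected 29.4, and strict rounding gives 33. Taken alone this would hardly merit a comment.

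What makes it worth correcting is that a target already just missed has no visible margin for motion exclusions. The effect is plainest for the controls, where a single failed scan takes the group below 30. The direction is clear from the article; the amount is not. The range of 28.6 to 26.5 usable patients per arm depends wholly on the assumed 3% to 10% failure rate.

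A reader might infer that the trial is too small or that enrolment must rise. The documents do not support that: the threshold is soft and no power target is stated that the lower numbers would breach.

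**What to change.** Keep 96 patients and 30 healthy controls, and make two changes.

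1. Restate the expected numbers in the Sample size calculation: about 29 per arm after 8% loss, with 30 kept only if loss does not exceed 6.25%, and fewer for imaging after motion exclusions. If a figure is given for the latter, attach its assumption: about 28.6 to 26.5 per arm if 3% to 10% of the remaining patients fail.
2. State that any control whose single scan fails the motion rule will be replaced, so that 30 usable controls are kept.

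Optionally, add the detectable VAS difference, given for the intention-to-treat set: about 0.71 SD at 32 per arm, rising to 0.75 SD if only about 29 completers carry the information, for an unadjusted pairwise test at two-sided 0.05 with 80% power.

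The cost is a text change, a slightly less favourable stated figure, and possibly a few replacement control scans.

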### Clinical outcome measures

#### Primary outcome

The primary outcome is the primary outcome is the intensity of the migraine attack, which will be assessed using a VAS score of 0–10. A headache diary form is designed to record details of each migraine attack, including its cause, duration, intensity, presence of aura, accompanying symptoms, frequency, and whether the migraine attack interfered with daily life and work, or emergency medication taken for unbearable pain. The headache diary form will be completed manually by the patient at the end of each migraine attack and will be monitored regularly by a dedicated researcher, who will collect and evaluate the data every 4 weeks (Supplementary File 4).

#### Secondary outcomes

Secondary outcomes include migraine attack frequency per month (−4 to 16 weeks), migraine attack days per month (−4 to 16 weeks), migraine attack intensity VAS score (8–16 weeks), duration of migraine (−4 to 16 weeks), emergency medication intake dose (−4 to 16 weeks), Migraine-Specific Quality of Life Questionnaire (MSQ) (−4 to 16 weeks), Migraine Disability Assessment Score (MIDAS) (−4 to 16 weeks), Headache Impact Test-6 (HIT6) (−4 to 16 weeks), Pittsburgh Sleep Quality Index (PSQI) (−4 to 16 weeks), Self-Rating Anxiety Scale (SAS) (−4 to 16 weeks), and Self-Rating Depression Scale (SDS), which are closely related to migraine. Blinding/reliability assessments will be conducted at the end of treatment (week 8) (Supplementary File 5), and treatment adherence evaluation will be assessed at the end of the follow-up period (week 16).

### MRI data

Magnetic resonance imaging data will be acquired within 1 week before the treatment and within 1 week after 8 weeks of treatment. The MRI will be acquired to avoid the patient’s migraine attacks, and all migraine patients should be without migraine (intermittent) for at least 72 h prior to the MRI scan before the scan is performed. Otherwise, the scan will be rescheduled. A Magnetic Resonance Scanner (3.0T GE Discovery 750; Milwaukee, WI, USA) with a 16-channel phased array head coil will be used, along with a restraining foam pad to minimize head motion and diminish scanner noise. The scans will be conducted at the Department of Radiology, the First Affiliated Hospital of Kunming Medical. Three-dimensional T1-weighted structural images will be obtained with the following scanning parameters: repetition time (TR) = 8.2 ms; echo time (TE) = 3.18 ms; field of view (FOV) = 256 mm × 256 mm; matrix = 512 × 512; in-plane resolution = 0.5 mm × 0.5 mm; slice thickness = 1 mm; 196 sagittal slices; flip angle = 9°. Resting-state functional MRI (rsfMRI) data will be collected within 7 min using the following parameters: TR = 2 s; TE = 30 ms; FOV = 240 mm × 240 mm; matrix = 64 × 64; in-plane resolution = 3.75 mm × 3.75 mm; slice thickness = 3.5 mm; 45 axial slices; flip angle = 90°, and 210 volumes will be acquired for each participant. Additional MRI data acquisition and preprocessing methods and procedures are described in Supplementary File 6.

### Seed-based FC analysis

The seed-based FC analysis will include all MWoA and HC participants and who completed the entire trial. PAG plays a pivotal role in the context of acupuncture for migraine treatment, so the PAG was chosen as the ROI for FC analysis. The location of the PAG seed will be selected based on previous studies (MNI coordinates: 0, −32, −12; size: 6 mm radius sphere) (Kucyi et al., 2013; Coulombe et al., 2017). The time course of each voxel in PAG will be extracted and averaged. Pearson correlation coefficients will be calculated between the average time series of PAG and each voxel throughout the whole brain. The obtained correlation coefficients will undergo Fisher-Z-transformed to increase normality. A clusterwise family-wise error rate (FWE) correction will also be considered.

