## Methods

### Study design

This randomized clinical trial was designed to evaluate the treatment effect and neurological mechanisms of CAT on MWoA. A total of 96 female MWoA participants and 30 female healthy controls (HCs) will be enrolled. The study will last 20 weeks including a 4-week screening phase (week −4 to week 0), an 8-week treatment period (weeks 1–8), and an 8-week follow-up period (weeks 9–16). The enrollment schedules, interventions, and assessments are summarized in Table 1. During the screening phase, participants will be assessed headache diaries. Clinical outcomes will be evaluated after treatment and during the follow-up. Multimodal MRI scans will be performed at baseline and after treatment. A study flowchart is presented in Figure 1.

**TABLE 1 T1:** Study schedule for data measurements.

	Study period					
	Enrolment	Allocation	Treatment phase		Follow-up	
Timepoint	−4 week	0 week	4 week	8 week	12 week	16 week

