### Clinical data analysis

Statistical analysis will be performed by independent statisticians who will have no knowledge of group allocation or the intervention process. Clinical outcomes will be analyzed using SPSS 28.0 statistical software (SPSS Inc., Chicago, IL, USA). All statistical analyses will adhere to the intention-to-treat principles. The missing data of participants who drop out will be handled using multiple imputation by chained equations (Azur et al., 2011), which can impute mixtures of continuous, binary, unordered categorical, and ordered categorical data. In addition, a per-protocol population analysis will be performed on participants who have completed at least 80 percent of their treatment protocol after randomization. Qualitative data will be presented as percentages [*n* (%)] and compared using the Chi-square (χ^2^) test. Quantitative data will be reported as means ± SDs and IQRs. Shapiro–Wilk tests will be performed to assess the normality of the data. Comparisons among the three groups will be analyzed using one-way analysis of variance (ANOVA), and non-parametric tests will be employed when the distribution is not normal. Outcomes will be analyzed using a one-way repeated measures ANOVA to evaluate the impact of time, group, and time × group interactions on migraine attacks. Comparisons of categorical data among groups will be examined using χ^2^ tests or Mann–Whitney U tests. All hypothesis tests will be two-tailed analyses, with statistical significance determined by a *p*-value < 0.05.

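### The connectivity analysis is limited to patients who finished the whole trial, on its plain reading week 16, although the planned analyses need no scan later than about week 9

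*Protocol article*

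**What the plan says.** The Seed-based FC analysis section fixes the population: "The seed-based FC analysis will include all MWoA and HC participants and who completed the entire trial". The phrase for completion is not defined further.

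On timing, Study design sets out 4 weeks of screening, 8 of treatment and 8 of follow-up. The end of the intervention text adds: "Follow-up visits will be conducted every 4 weeks throughout the study, up to week 16". The MRI data section says: "Magnetic resonance imaging data will be acquired within 1 week before the treatment and within 1 week after 8 weeks of treatment". Table 1 marks MRI at weeks 0 and 8 only. For healthy controls, Interventions says "brain imaging data will be collected only once".

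Neuroimaging data analysis then lists the connectivity analyses: a baseline comparison of patients with controls; a mixed ANOVA of time (baseline, after treatment) by treatment (three arms); paired t-tests within each arm; and correlations of change in connectivity with change in VAS.

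Clinical data analysis states: "All statistical analyses will adhere to the intention-to-treat principles". It adds: "The missing data of participants who drop out will be handled using multiple imputation by chained equations". It also defines a per-protocol set by completion of at least 80% of treatment.

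**The concern.** The rule asks for more than the analyses use. A patient who leaves in week 12 has both scans and would still be left out. A patient who leaves in week 5 has a valid baseline scan and would be left out of a baseline comparison that has nothing to do with treatment.

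Whether a patient stays to week 16 is decided after randomisation and may depend on response or tolerability. If late loss differs between arms, the arms in the mixed ANOVA are no longer quite the randomised ones. That ANOVA carries the trial's second aim, the mechanistic comparison of CAT with sham CAT and IAT. The sample size was also set from imaging considerations, so each usable scan pair counts.

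Finally, completers to week 16 are neither the intention-to-treat set nor the 80%-of-treatment per-protocol set. Taken literally, the sentence on intention to treat covers every analysis, and no section exempts imaging.

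**Working it through.** **1. What each analysis needs**

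| Analysis (Neuroimaging data analysis) | Data needed | Week-16 completion needed? |
|---|---|---|
| Patients vs controls, baseline | baseline scan | no |
| Time × treatment mixed ANOVA | baseline and post-treatment scans | no |
| Paired t-tests within arm | the same two scans | no |
| Correlation with VAS change | two scans and VAS change | not stated; no, if VAS change covers the scan interval |

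**2. The plan's own figure**

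Inputs (Sample size calculation): 30 per group, 8% loss, 32 per group, 96 in total.
- 30 × 1.08 = 32.4, which rounds to the stated 32.
- 30 / (1 − 0.08) = 32.6, which rounds up to 33.

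The stated 32 is reproduced to within one patient. The article gives no power figure to reproduce.

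**3. Patients left by the completer rule**

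Take 8% as the loss by week 16.
- Lost: 96 × 0.08 = 7.68.
- Completers: 96 × 0.92 = 88.3, or 29.4 per arm.

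**4. Valid scan pairs discarded**

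Let f be the share of losses that occur after the second scan. The document does not give f.
- Pairs discarded = 7.68 × f.
- Pairs available without the rule = 96 − 7.68 × (1 − f).

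| f | Pairs discarded, total (per arm) | Pairs available without the rule, total (per arm) |
|---|---|---|
| 0 | 0 (0) | 88.3 (29.4) |
| 7/16, even loss over 16 weeks, second scan at week 9 | 3.4 (1.1) | 91.7 (30.6) |
| 1 | 7.7 (2.6) | 96 (32) |

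With heavier loss and the same even spread (assumptions):
- 15% loss: 32 × 0.85 = 27.2 completers per arm, against 32 × (1 − 0.15 × 9/16) = 29.3 with both scans.
- 20% loss: 25.6 against 28.4.

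**5. Baseline comparison with controls**

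All 7.68 dropouts, about 8, lose a usable baseline scan, assuming each was scanned before treatment. The effect on the standard error, up to the common SD, is:
- all 96 patients vs 30 controls: √(1/96 + 1/30) = 0.209
- 88 patients vs 30 controls: √(1/88 + 1/30) = 0.211

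The increase is about 1%.

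These counts ignore scans lost to head motion, which affect either rule.

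**The case against.** **The phrase may not mean week 16.** The sentence is garbled and also covers controls, who are scanned once and have no follow-up. For them it can only mean completing their own imaging. Applied to patients, that reading requires both scans, and no scan pair would be lost. This is possible, but it is not what the words say. It would also still drop patients who left before the second scan from the baseline comparison: 7.68 × 9/16 = 4.3 patients under even loss.

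**A reader might infer a flat contradiction of the intention-to-treat rule.** The document does not establish that. The rule stands under Clinical data analysis, next to the choice of software for clinical outcomes and a chained-equations method suited to clinical variables. Imaging has its own section, which mentions neither intention to treat nor imputation. The conflict is with the literal wording, and its scope is unclear.

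**A reader might infer that the between-arm result is biased.** No dropout reasons or rates by arm are given, so bias is a possibility of unknown size and direction. The argument about randomised arms does not apply to the comparison with controls, which is not randomised. The primary outcome is clinical and is not affected.

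**A reader might infer that the discarded pairs exceed the attrition allowance.** If half of the losses came in follow-up, 7.68 × 0.5 = 3.8 pairs would go in total, or 1.3 per arm. The allowance is 2 per arm, or 6 in total. Only if more than 6 / 7.68 = 78% of losses came after the second scan would the discarded pairs alone exceed it. The completer shortfall below 30 per arm comes from rounding 32.6 down to 32, since 33 × 0.92 = 30.4.

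**Some restriction is unavoidable.** A paired analysis cannot use a patient without a second scan. That justifies requiring both scans for the treatment analysis, but not requiring week 16. Scans may also be moved if the patient was not attack-free ("Otherwise, the scan will be rescheduled"), so week 9 is approximate and f could be somewhat lower than 7/16.

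**Conclusion.** The point holds as a poorly chosen analysis set. As written, the connectivity analysis selects on completion of follow-up, which none of its scan comparisons needs. At the planned 8% loss the cost is modest: 0 to 7.7 scan pairs in total, about 3.4 under evenly spread loss. In that case the treatment analysis would have 30.6 patients per arm without the rule instead of 29.4 with it, on either side of the 30 relied on. In the control comparison the loss is about 8 baseline scans and about 1% in precision.

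The stronger reason to change is that the rule opens the mechanistic between-arm comparison to selection if late loss differs by arm. These conclusions rest on reading completion as week 16, taking 8% as loss by that week, and assuming when losses occur. Actual bias and a definite breach of the intention-to-treat rule are not shown.

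**What to change.** Replace the sentence in Seed-based FC analysis with two definitions:

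- (a) Baseline comparison of patients with controls: every participant with a usable baseline scan.
- (b) Treatment analysis: every randomised patient with usable baseline and post-treatment scans, in the arm assigned, regardless of later follow-up.

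Keep trial completers as a sensitivity analysis. In Clinical data analysis, state whether the intention-to-treat rule is meant to cover imaging. A longitudinal mixed model that also uses patients with one scan is optional.

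The cost is one replaced sentence and one clarification. No new data, scans or staff are needed.
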